##### REMINDER4carers arm

This experimental arm is offered only to MCI participant’s caregivers, who will receive ten parallel psychoeducation and support sessions alongside the delivery of the REMINDER program to the patients. Sessions will be delivered weekly, in groups of 5–8 caregivers, lasting approximately 60 min each, either face-to-face or virtually depending on caregiver’s availability. The sessions will provide emotional support and guidance on caregiving topics such as changing roles, uncertainty of care needs, future and long-term planning, caregiver well-being and self-care, communication skills, and grief and loss.

Research also indicates that increasing caregivers’ awareness of patients’ needs and promoting supportive behaviors enhances patients’ adherence and engagement in protective health behaviors (e.g [35]).,. Moreover, caregivers themselves are at increased risk of cognitive decline and dementia due to chronic stress and caregiving burden [50]. These sessions also aim to promote caregivers’ own well-being and resilience, indirectly supporting their cognitive health.

##### Waiting list control groups

A waitlist control design was selected to ensure provision of the intervention to all participants while allowing comparison with a no-intervention condition over the 6-months follow-up period. After the 6-month follow-up period, participants in the control group will receive the REMINDER intervention, which can be attended either in-person or via videoconferencing, depending on participants’ preference and logistical considerations. Participants’ engagement in other active interventions during the 6-month study period will be monitored through regular follow-up contacts.

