### Objectives

Therefore, our aims are:

Primary outcomes.

To test the efficacy of the REMINDER program in improving global cognition and protective lifestyle behaviors (e.g., physical activity, diet, social engagement, sleep hygiene, cognitive stimulantion, and regular health monitoring) in individuals at risk of dementia (community-dwelling or MCI) at immediate, short- and long-term follow-up.

Secondary outcomes.

To examine the efficacy of the REMINDER program on neuropsychological functioning, including emotional, cognitive, and functional domains;To evaluate the additive effect of including REMINDER4Carers to the REMINDER program on lifestyle behavior, cognition, and well-being of MCI patients;To examine the effects of the REMINDER program on markers of neurodegeneration (blood-based biomarkers and neuroimaging markers).

Exploratory outcome.

To monitor diagnostic transitions in the MCI subgroup (conversion to dementia) across the 18-month follow-up, and examine whether participation in REMINDER alone or and REMINDER with caregiver support may delay progression compared to the waiting list control.

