#### Hypotheses

We hypothesize that REMINDER participants will exhibit significant and sustained positive changes in lifestyle behaviors and global cognition, compared to the waitlist control group. For a subset of MCI participants, we will offer an additional condition involving the patient’s partner’s participation in REMINDER. We hypothesize that this complementary support (REMINDER4Carers) will lead to greater improvement in the primary outcome compared to REMINDER alone, according with evidence highlighting the role of care partners in behavior change interventions [22, 24]. We anticipate positive impacts in secondary psychosocial and cognitive aims as well. Additionally, in the MCI subgroup, we hypothesize that participation in REMINDER (with or without care partner involvement) will be associated with a lower rate of diagnostic transition to dementia across the 18-month follow-up.

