##### Primary outcome

Given the multidomain nature of this intervention, we will consider as primary outcomes the following:A *cognitive function composite *(z-score) will be calculated from the total Mini Mental Status Exam (MMSE) score [53], Word List Total Recall Score (WMS-III) [54], Category Fluency total [55], and Trails Part B [56], providing a measure of global cognitive function.*Healthy lifestyle behaviors*, measured with Healthy Lifestyle Assessment Toolkit (HLAT) [57]. This will measure adherence to physical activity, cognitive engagement, and diet and will be complemented with qualitative interviews for a subsample of participants. These outcomes will be measured in all assessment time points (pre-, post-, 3-, 6-, and 18- months follow-up).

These outcomes will be measured in all assessment time points (pre-, post-, 3-, 6-, and 18- months follow-up).

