Conversion from MCI to dementia across the 18-month follow-up, assessed via clinical evaluation and standardized cognitive assessments (e.g., ACE-R, MMSE, clinical interview). This outcome will allow examination of whether participation in REMINDER alone or REMINDER with caregiver support delays progression compared to the waiting list control.

**Table 2 Tab2:** *Measures*,* psychometric properties*,* and timepoints of assessment*

Construct and measure	Scoring	Criteria/Psychometric properties	Timepoint
Demographic characteristics			
Age, gender, education level, professional status, marital status	—	—	Screening
Clinical characteristics			
Presence of medical diagnosis, actual medication, sensory issues, mobility deficits, use of substances, previous issues and hospitalization, and Lifestyle for Brain Health (LIBRA) score [51]	LIBRA score: range from − 5.9 to 12.7	LIBRA score: higher = more risk	Screening
Primary Outcome			
* Cognitive function composite*			
Mini-mental State Examination (MMSE)	Total 0–30	Higher scores indicating better functioning	Baseline, post, 3, 6, and 18-month follow-up
Word List (WMS-III)	Sum of recalled words	Internal consistency 0.67 to 0.90 (median = 0.83)	Baseline, post, 3, 6, and 18-month follow-up
Verbal Fluency (letters and animals)	Number of correct words in 60s	Excellent reliability: α = 0.89; ICC = 0.996	Baseline, post, 3, 6, and 18-month follow-up
Trail Part B	Time to completion (sec)	Higher times = worse performance	Baseline, post, 3, 6, and 18-month follow-up
* Health lifestyle behaviors*			
Healthy Lifestyle Assessment Toolkit (HLAT)	Traffic light rating system for 8 lifestyle components: low risk (green), moderate risk (yellow), relevant risk (orange)	—	Baseline, post, 3, 6, and 18-month follow-up
Secondary outcome			
* Specific cognitive functions*:			
Addenbrooke’s Cognitive Examination – Revised (ACE-R)	Total 0–100 (with 5 subdomains)	Higher scores indicating better functioning; Excellent internal consistency (Cronbach’s α = 0.95)	Baseline, post, 3, 6, and 18-month follow-up
Behavior Rating Inventory of Executive Functions - Adults (BRIEF-A)	3-point Likert scale (1 = Never; 2 = Sometimes; 3 = Often), frequency of behaviors in the past month	Indexes and Global Executive Composite: α = ≥0.90 (very good); Scales: α = 0.70–0.80.70.80 (acceptable) or α = ≥0.80 (good)	Baseline, post, 3, 6, and 18-month follow-up

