#### Participants

This study follows a randomized, waitlist-controlled design. Eligible participants will be invited to complete the baseline assessment. Recruitment will target individuals presenting modifiable dementia risk factors, as well as caregivers/relatives of MCI patients, who will be included in a dedicated experimental arm of the Clinical Trial. Following baseline assessment, participants will be randomly assigned to one of the study arms: *Community Trial –* REMINDER face-to-face, REMINDER virtual, or Waitlist Control (Fig. 2, trial flowchart); *Clinical Trial –* REMINDER intervention alone, REMINDER plus caregiver support, or Waitlist Control (Fig. 3, trial flowchart). A researcher blind to the assessment procedure will conduct randomization, and then all participants will be informed about their assigned condition. Waitlist participants will be offered the REMINDER intervention after 6 months, while all participants will be followed for 18 months post-intervention (24 months total).

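### The waitlist starts REMINDER after 6 months, so the 18-month comparison with it is early versus delayed REMINDER, not REMINDER versus no intervention

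*Protocol article*

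**What the plan says.** **The untreated window.** Waiting list control groups justifies the design as "allowing comparison with a no-intervention condition over the 6-months follow-up period" and continues: "After the 6-month follow-up period, participants in the control group will receive the REMINDER intervention". The Participants section says: "Waitlist participants will be offered the REMINDER intervention after 6 months". The same sentence follows everyone for 18 months after the intervention and gives 24 months in total.

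**The long-term aims.**
- The primary objective covers cognition and lifestyle "at immediate, short- and long-term follow-up", and the Primary outcome section measures both at every visit up to 18 months.
- The Hypotheses section expects sustained change in both primary outcomes relative to the waitlist. For MCI it expects a "lower rate of diagnostic transition to dementia across the 18-month follow-up".
- The Secondary outcomes section says that conversion across the 18-month follow-up will show "whether participation in REMINDER alone or REMINDER with caregiver support delays progression compared to the waiting list control". The exploratory aim under Objectives makes the same comparison. The Abstract, Objectives and Table 2 call this outcome exploratory, although it is also described under Secondary outcomes.

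**The analysis.** Statistical methods plans linear mixed models with a time-by-group interaction, and Markov models for diagnostic transitions. It does not mention the switch, a restriction to visits before it, or a different meaning of the group contrast afterwards.

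**The concern.** One section ends the no-intervention comparison at 6 months, while others carry the waitlist forward as comparator to 18 months. Once the waitlist has had REMINDER, the arms differ in when they received it, not in whether they did.

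The result could then mislead in either direction. If REMINDER works and its effect lasts, the treated waitlist catches up, and the small 18-month difference may be read as loss of effect. If the effect fades, a more recently treated waitlist may do better than the early arms, and the sign may reverse. Neither result answers the question that the objectives and hypotheses pose. Both trials share this design, so both primary outcomes are affected in each, as is conversion in the Clinical Trial.

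In the Clinical Trial the waitlist is to receive REMINDER, with no mention of caregiver sessions. The late contrast between the caregiver arm and the waitlist therefore also mixes timing with content.

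**Working it through.** **1. The planned sample size reproduces and is not at issue.** One-way omnibus F test, three arms, f = 0.20, alpha 0.05 (assumed, since the protocol gives none). With N = 244 the noncentrality is 244 × 0.20² = 9.76 on 2 and 241 degrees of freedom, and power is 0.8002. With 10% added, 244 × 1.1 = 268, rounded to 270, or 90 per arm. The calculation has one effect size and makes no allowance for a control arm treated before the last visit.

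**2. When is the waitlist untreated?** The 18-month clock can be read in two ways:
- Reading A, counted from baseline: switch at 6 months (0.5 year), last visit at 18 months (1.5 years).
- Reading B, counted from the end of the 10-week course (10/52 year, 2.3 months): switch at 8.3 months (0.692 year), last visit at 20.3 months (1.692 years).

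On either reading the waitlist is untreated at the post, 3- and 6-month assessments, and at 18 months the switch is 12 months past.

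**3. Share of control conversions after the switch.** Inputs: 90 MCI controls (Trials design, Sample size) and an annual conversion rate p of 10 to 15% (Background and rationale, where it refers to conversion to Alzheimer's). Expected conversions by time T in years are 90 × (1 − (1 − p)^T). The share after the switch is the later count minus the earlier one, divided by the later one. The control rate is held at its untreated value throughout, and there is no dropout.

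| Reading | p | By switch | By last visit | Share after switch |
|---|---|---|---|---|
| A | 10% | 4.6 | 13.2 | 65% |
| A | 15% | 7.0 | 19.5 | 64% |
| B | 10% | 6.3 | 14.7 | 57% |
| B | 15% | 9.6 | 21.6 | 56% |

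Example (A, 10%): 90 × (1 − 0.9^0.5) = 4.62, 90 × (1 − 0.9^1.5) = 13.16, and (13.16 − 4.62)/13.16 = 65%. If the stated 24-month total were the window, with the switch at 6 months, the share would be 72 to 73%.

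**4. How much of a conversion difference would remain.** Assumptions that the protocol does not make: a constant hazard h = −ln(1 − p), a hazard ratio of 0.5 from the start of REMINDER, full waitlist uptake, and an equal and immediate effect once treated. With switch time S and end time T:
- untreated control: 1 − exp(−hT)
- early arm: 1 − exp(−0.5hT)
- switched waitlist: 1 − exp(−hS − 0.5h(T − S))

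Reading A, p = 10%: 14.6%, 7.6% and 10.0%. The difference from the early arm falls from 7.0 to 2.4 points. At p = 15% it falls from 10.2 to 3.5 points. Reading B gives 7.8 to 3.3 and 11.2 to 4.8 points. About 34 to 43% of the difference remains. An assumed hazard ratio of 0.7 leaves a similar 34 to 42%.

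**5. Primary outcomes.** No effect trajectory is given, so only the direction can be stated. If the treated waitlist responds as the early arms did and the effect lasts fully, the expected 18-month difference is about zero. If the effect decays with time since the course, the waitlist is nearer to its own course and the difference may favour it.

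**The case against.** Several points can fairly be made for the plan, and most limit how far the criticism goes.

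- **The untreated window is stated.** The plan limits the no-intervention comparison to 6 months and nowhere calls the waitlist untreated at 18 months. A reader might infer that it does. What stands is that no section on the late comparison acknowledges the switch.
- **A control remains.** A reader might infer that no control group exists at 18 months. The design does not support that. Early versus delayed REMINDER is randomised, as are REMINDER versus REMINDER with caregiver support and face-to-face versus virtual.
- **The explicit clash is in an exploratory outcome.** Conversion is labelled exploratory. For the primary outcomes, the objective says long-term without naming a comparator, the visit list names none, and the sustained-benefit hypothesis gives no month. The 18-month waitlist contrast on the primary outcomes has to be put together from these sections. It is the natural reading, and nothing shown rules it out.
- **Pooling of visits is not stated.** A reader might infer that the model averages all visits, so that the switch also weakens the earlier comparisons. The plan says only time-by-group interaction. With visit as a factor, the post, 3- and 6-month contrasts can be estimated without that dilution. A power loss computed for an average would describe an analysis that the plan does not state.
- **The clock is ambiguous, not shown to be wrong.** The Participants section gives no origin for its 6 months. If it means baseline while visits run from the end of the course, the switch could come before an assessment at 8.3 months. Waiting list control groups, however, places it after the 6-month follow-up period, and the shorter phrase may be shorthand for that.
- **Uptake may be partial.** The Participants section says that REMINDER is offered, so the dilution may be smaller than in step 4.

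**Conclusion.** The concern holds as a conflict between the design and the stated long-term aims. After 6 months there is no untreated control. The 18-month contrast with the waitlist is early versus delayed REMINDER, so neither sustained benefit nor delayed progression relative to no intervention can be concluded from it.

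About 56 to 65% of control-arm conversions would fall after the switch on the two 18-month readings. This rests on the background conversion rate, an unchanged control rate and no dropout, and it is an illustration rather than a forecast. The shrinkage to about a third or two fifths of a conversion difference also needs an assumed hazard ratio and full uptake. For the primary outcomes the documents support a direction of bias but no figure.

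The comparison with the waitlist through 6 months is sound, provided that the 6-month assessment comes before the switch.

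**What to change.** 1. Limit efficacy contrasts with the waitlist, for both primary outcomes and for conversion, to assessments before the waitlist's own REMINDER start (post, 3 and 6 months). Exclude later waitlist data from that model.
2. Label any 18-month contrast with the waitlist, including conversion, as early versus delayed start. Reword the long-term objective, the exploratory aim, the hypotheses and the conversion text under Secondary outcomes to match.
3. At 18 months keep REMINDER versus REMINDER with caregiver support as the randomised contrast for its stated hypothesis. Report face-to-face versus virtual descriptively, since no objective or hypothesis is stated for it.
4. Reconcile Waiting list control groups with Participants on the origin of the 6 months, and the 18 months post-intervention with the 24-month total, so that the waitlist's 6-month assessment plainly precedes its switch.

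The cost is rewording and model specification. The sample size of 244 (270 with dropout) stays. The long-term claim against no intervention is given up, but the design cannot support it.

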#### Outcomes

The professional qualified to conduct pre-and post-intervention neuropsychological assessment will be blind to the intervention arm each participant was assigned. Participants will be assessed at baseline, post-intervention, and at 3, 6, and 18-month follow-up. The endpoint times were selected to capture immediate, short-term, and long-term effects of the REMINDER program on cognitive and lifestyle outcomes, in line with previous multidomain dementia prevention trials.The REMINDER protocol will include a comprehensive protocol of both cognitive, emotional, and functional status (Table 2). The protocol lasts approximately 1-hour session. All assessments will be completed by participants. Care partners will support adherence, provide collateral information when relevant (e.g., diagnostic transitions), and complete the informant version of the BRIEF-A [52]. In addition, they will answer a brief post-intervention satisfaction questionnaire to capture their views on the program’s relevance and utility.

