##### Secondary outcomes

The secondary outcome, assessed at baseline, post-intervention, and at 3-, 6-, and 18- months follow-up, will include:

*Specific cognitive functions* – individual cognitive measures that contribute to the primary cogniticve composite will also be analyzed separately to examine specific domans. These include:Global Cognition (Addenbrooke’s Cognitive Examination – Revised [58]); Episodic memory (Word List) [54]; Verbal Initiative (Letters P, M, R and Categories Animals Fluency) [55]; Executive Function (Behavior Rating Inventory of Executive Functions- Adults (BRIEF-A) [52]; Working Memory (Weschler Adult Intelligence Scale (WAIS) – Digit Span Task) [59].*Perceived and performance-based functional status*:Adults and Older Adults Functional Assessment Inventory (IAFAI) [60]; University of California San Diego Performance-Based Skills Assessment (UPSA Brief) [61]. *Psychosocial/Mental Health indicators*:Geriatric Depression Scale (GDS-30) [62]; World Health Organization Quality of Life (WHOQOL-OLD 7) [63]; Lubben’s Brief Social Network Scale [64]; Psychological change (Clinical Outcome Routine Evaluation) [65]; Motivation (Motivation to Change Lifestyle and Health Behaviour for Dementia Risk Reduction (MCLHB-DRR) [66].*Biological markers of neurodegeneration (assessed at baseline, post-intervention): *Currently, the most robust blood-based biomarker is the neuronal cytoplasmic protein Neurofilament light chain (NfL). NfL is a sensitive but unspecific marker of axonal injury, with potential ability to rule-in or rule-out neurodegeneration and to assess its progression rate [67]. Therefore, the value of baseline and/or longitudinal measurements of blood NfL in predicting the course of cognitive decline has been verified in different neurodegenerative dementias, and in cognitively normal individuals [68]. Importantly, since blood NfL can detect axonal damage that has occurred in the last 3 months, it has also been used as an indicator of the treatment efficacy of disease-modifying treatments [69]. Other recognized important markers are neuroinflammation and cerebrovascular function alterations and/or blood-brain barrier (BBB) damage. Glial fibrillary acidic protein (GFAP), an intermediate filament protein mainly expressed in astrocytes of the central nervous system and soluble platelet-derived growth factor receptor-β (sPDGFRβ) a marker of BBB-associated capillary mural cell pericyte, respectively, are good candidates [70]. Such markers have also recently shown potential as early surrogates of cognitive dysfunction [71–73]. We will assess the levels of blood NfL, GFAP and sPDGFRβ in a subset of the study population (33% in all study arms) before and after the intervention period. Blood samples will be collected into serum separation tubes, centrifuged at 1500 g, 4^o^C for 10 min. Serum will be separated, aliquoted and frozen at –80^o^C in the same day of collection. Serum NfL and GFAP will be quantified simultaneously using the SiMoA (Single Molecule Array) Neuro-2Plex B multiplex kit in an SR-X platform (Quanterix, USA). Serum sPDGFRβ levels will be determined separately using an already described ELISA kit.*Diagnostic transitions in MCI:*

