* Diagnostic transitions*	Conversion from MCI to dementia	Assessed via clinical evaluation, standardized cognitive assessments (ACE-R, MMSE, clinical interview).	Baseline, post, 3, 6, and 18-month follow-up

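### In the Clinical Trial, informant BRIEF-A ratings and collateral information on conversion come from care partners who are themselves treated in the REMINDER4Carers arm only, and no safeguard is stated

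*Protocol article*

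**What the plan says.** The Outcomes section gives care partners a part in outcome measurement: "Care partners will support adherence, provide collateral information when relevant (e.g., diagnostic transitions), and complete the informant version of the BRIEF-A". The sentence just before it reads "All assessments will be completed by participants", so the text does not make clear how self-report and informant forms are combined.

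The Secondary outcomes section lists "Executive Function (Behavior Rating Inventory of Executive Functions- Adults (BRIEF-A" without naming a version. Table 2 also names none and schedules BRIEF-A at baseline, post-intervention and 3, 6 and 18 months.

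Conversion from MCI to dementia is "assessed via clinical evaluation and standardized cognitive assessments (e.g., ACE-R, MMSE, clinical interview". Table 2 schedules it at the same visits and labels it exploratory.

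The REMINDER4carers section describes an arm of the Clinical Trial for the caregivers of MCI participants, "who will receive ten parallel psychoeducation and support sessions alongside the delivery of the REMINDER program to the patients". Part of its rationale is that "increasing caregivers’ awareness of patients’ needs and promoting supportive behaviors" improves patients' adherence and engagement.

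The Objectives include: "To evaluate the additive effect of including REMINDER4Carers to the REMINDER program on lifestyle behavior, cognition, and well-being of MCI patients".

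The Outcomes and Blinding sections describe only the professional assessor as blind. The Participants section says that participants are told their condition. Informants are not mentioned in this respect.

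**The concern.** What separates the two active arms of the Clinical Trial is a treatment given to the people who complete the informant questionnaire. A blinded neuropsychologist cannot correct for this, because the rating is the care partner's own.

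Sessions that raise awareness of the patient's needs could lead a care partner to report more problems. Support and better coping could lead the same person to report fewer. Either can happen with no change in the patient, so the sign of the bias cannot be predicted.

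Conversion is exposed more weakly. Collateral information is gathered as the need arises and not on a common schedule. Care partners in one arm have had ten sessions that may change what they notice or mention. Ascertainment could then differ between that arm and waitlist.

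At stake is part of the additive-effect objective, which includes cognition and well-being, and one input to the exploratory conversion comparison.

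**Working it through.** **The plan's own figure.** The Sample size section gives 244 before dropout for the Community Trial and applies the same analysis to the Clinical Trial. A one-way ANOVA with 3 groups, f = 0.20, power 0.80 and alpha 0.05 (not stated, so assumed) gives a smallest total of 244 (power 0.8002). The plan's figure reproduces. It concerns the primary outcomes and is not affected by this point. After the plan's 10% dropout, 90 per arm becomes 90 × 0.90 = 81.

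**Which contrasts are exposed (Clinical Trial).**

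| Contrast | Care partners treated? | Informant BRIEF-A exposed? |
|---|---|---|
| REMINDER4Carers vs REMINDER alone | one side only | yes |
| REMINDER4Carers vs waitlist | one side only | yes |
| REMINDER alone vs waitlist | neither side | not by this route |

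For conversion, the Objectives and Secondary outcomes specify comparison of each active arm with waitlist. The exposed comparison is therefore REMINDER4Carers vs waitlist.

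**Size for informant BRIEF-A.** The documents give no figure for an informant shift, so δ is assumed to be 0.1 to 0.3 SD with no true patient difference. The test is an unadjusted two-sided two-sample t test at 5% at one visit, with n per arm:

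- SE of the difference = √(2/n): √(2/81) = 0.157 SD; √(2/90) = 0.149 SD.
- Noncentrality = δ/SE; degrees of freedom = 2n − 2.
- False-positive rate = P(|T| > critical value) under the noncentral t.

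| δ (SD) | δ/SE, n = 81 | Rate, n = 81 | δ/SE, n = 90 | Rate, n = 90 |
|---|---|---|---|---|
| 0 | 0 | 5.0% | 0 | 5.0% |
| 0.1 | 0.64 | 9.7% | 0.67 | 10.2% |
| 0.2 | 1.27 | 24.4% | 1.34 | 26.6% |
| 0.3 | 1.91 | 47.5% | 2.01 | 51.7% |

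Normal check at n = 90, δ = 0.2: Φ(1.34 − 1.96) = Φ(−0.62) ≈ 0.27, which agrees.

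**Size for conversion.** The Background gives 10 to 15% a year from MCI to Alzheimer's disease. Over 18 months:

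- 1 − 0.90^1.5 = 14.6%
- 1 − 0.85^1.5 = 21.6%

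If ascertainment in one arm were 20% higher in relative terms (an assumption), the spurious difference would be 0.20 × 14.6 = 2.9 to 0.20 × 21.6 = 4.3 percentage points. With 81 per arm such a difference would be significant in about 7 to 9% of trials, so this part of the problem is small.

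**The case against.** The strongest case against is that little of the trial is touched, and much of that case stands.

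- **Primary outcomes.** The Hypotheses tie the comparison of REMINDER4Carers with REMINDER alone to the primary outcome. The cognitive composite is performance-based, and no informant role is stated for HLAT. The main test of additive effect is not reached by this bias.
- **Which BRIEF-A is the endpoint.** A reader might infer that the executive-function endpoint is itself informant-rated. The documents do not establish this, since no version is named. If a self-report form is collected and used, the bias is confined to the informant form.
- **Trails B.** A reader might infer that no blinded performance measure of executive function is planned, because Trails B is missing from the list of specific functions. The sentence opening that list says the components of the composite will also be analysed separately, and Trails B is one of them.
- **Conversion criteria.** Table 2 gives the inputs as "Assessed via clinical evaluation, standardized cognitive assessments (ACE-R, MMSE, clinical interview", and a reader might infer that functional measures are excluded. The Secondary outcomes text introduces the same inputs as examples, so exclusion cannot be concluded. Transitions are already scheduled at every visit in all arms, and collateral information only supplements the assessor's evaluation. Nothing says that the caregiver sessions feed information into ascertainment.
- **Size of the shift.** It is assumed, and the listed session topics include no training in rating executive symptoms. At 0.1 SD the false-positive rate only about doubles.

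An unblinded informant is also unavoidable when the caregiver is treated. That is a reason to limit the weight placed on the informant's rating. It does not remove the bias.

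**Conclusion.** The point holds in a limited form. In the Clinical Trial, informant BRIEF-A contrasts involving the REMINDER4Carers arm cannot be attributed to the patient alone, and the direction of the bias is unknown. The exploratory conversion comparison of that arm with waitlist is affected in part, through collateral information that is not collected on a common schedule.

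The false-positive rates, about 10% to 48% with 81 per arm (10% to 52% with 90), illustrate a 0.1 to 0.3 SD informant shift. They do not estimate what will happen. They rest on that assumed shift, a 5% two-sided test and a single-visit comparison without baseline adjustment.

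The documents do not support the wider conclusion that the trial's executive-function endpoint, its primary comparisons or its conversion definition are unsound. BRIEF-A is a secondary measure and conversion is labelled exploratory, so this is an improvement worth making and does not threaten the main result.

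**What to change.** 1. State which BRIEF-A version is the secondary outcome. For any contrast involving the REMINDER4Carers arm, treat the informant version as supportive only.
2. For those contrasts, rest executive-function conclusions on Trails B. It is already collected at every visit, performance-based, given by the blinded assessor and planned for separate analysis.
3. Replace collateral information given as the need arises with the same short set of questions, put to every care partner at each scheduled visit in all three arms. The eligibility criteria require an available caregiver for every MCI participant, so this is feasible in each arm.
4. Add a sensitivity analysis of conversion that excludes care-partner information.

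The cost is protocol wording, a few routine questions per visit and less weight on informant BRIEF-A. No new instrument or visit is needed. Item 3 has to be settled before data collection, because collateral information not asked for in some arms cannot be recovered by a later analysis decision.
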